**1. BACKGROUNDS AND RATIONALE**

Rifabutin is commonly used for human immunodeficiency virus (HIV)-associated mycobacterial infections, especially during highly active antiretroviral therapy (HAART) containing HIV protease inhibitors (PIs), since it is less likely to induce hepatic microsomal enzymes than rifampicin. Ethnic differences may alter the dose required to achieve a particular concentration of the drug in the circulation, while there are no such pharmacokinetic studies for rifabutin use in Asians.

The present study was conducted to evaluate the pharmacokinetics of rifabutin in Japanese patients with HIV-1-related mycobacterial infection when used alone at 300 mg/day without HAART and at 150 mg every other day when used in combination with protease inhibitors.

**2. OBJECTIVES**

**# Primary objective**

To evaluate the pharmacokinetics of rifabutin in Japanese HIV-infected patients.

**# Secondary objective**

To investigate the impact of protease inhibitors on the pharmacokinetics of rifabutin in Japanese HIV-infected patients.

**3. STUDY DESIGN**

An open-label pharmacokinetic study with two arms

**4. METHODS**

**4.1 Inclusion criteria**

Japanese HIV-infected individuals over 20 years of age who receive rifabutin-containing anti-mycobacterial therapy at National Center for Global Health and Medicine (formerly, International Medical Center of Japan, IMCJ) and provide written informed consent.

**4.2 Exclusion criteria**

- Abnormal liver function tests [aspartate aminotransferase (AST), alanine aminotransferase (ALT) or total bilirubin (>3 times the upper limit of normal: ULN)],

- Renal dysfunction (creatinine clearance <30 ml/min)

- During pregnancy or breastfeeding

**4.3 Study group and sample size**

**Group I** (10 patients): Rifabutin 300 mg/day without HAART

**Group II** (10 patients): Rifabutin 150 mg/day every other day combined with PI containing HAART

Since the average number of HIV-positive mycobacterium cases at NCGM is around ten per year, at least 10 for each study arm is expected if the sequential enrollment of a patient into both groups is achieved in most participants.

**4.4 Study period**

**Enrollment:** from February 2008 and March 2009.

**Follow-up observation:** two years after discontinuation of rifabutin use.

**4.5 Demographic and Clinical data**

Demographic and clinical information will be collected in all participants as followings; age, gender, route of HIV-1 infection, body weight, height, CD4+ T lymphocyte count, HIV-1 plasma viral loads, HBs antigen, anti-HCV antibody, AST, ALT, total bilirubin, serum creatinine, and any adverse events of grade 2 or greater from the commencement of rifabutin use until two years after discontinuation of rifabutine use.

**4.6 Pharmacokinetic assays**

Pharmacokinetic sampling will be done after at least 5 days of rifabutin-containing anti-mycobacterial therapy without (Group I) or with (Group II) HAART. Blood samples will be collected just before rifabutin administration and then 0.5, 1, 2, 4, 6, 8 and 24 hours afterward. Patients of Group II treated with 150 mg of rifabutin every other day will undergo additional sampling at 48 hours.

The plasma concentrations of rifabutin and its major metabolite, 25-*O*-desacetyl rifabutin will be determined simultaneously by validated high-pressure liquid chromatography (HPLC). Blood samples will be taken in heparin-containing tubes, placed on ice and centrifuged at 3000 x *g* for 10 min. Then, the obtained plasma will be deproteinized by using three times volume of methanol and centrifuged 15,000 x *g* for 5 min, and the supernatant will be used for assay.

The area under the curve (AUC) will be calculated using non-compartmental techniques (WinNonlin, ver. 5, Pharsight Corp., Mountain View, CA) based on the obtained values (AUC 0-24 h for all, AUC 0-48 h for Group II). The maximum plasma concentration (C_max_) and time of C_max_ (T_max_) will be determined directly from the data.

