**4.7 Statistical analysis**

Differences between groups were determined by using the Fisher’s exact test for categorical data and the Mann Whitney’s test for continuous variables. For all statistical analyses, differences were considered significant if the *p* value was less than 0.05.

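### No parameter is named for the protease-inhibitor comparison, and the only AUC defined for both groups, raw AUC0-24, mixes the inhibitor effect with dose and dosing interval

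*Protocol*

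**What the plan says.** Section 4.3 of the Protocol sets the two regimens: "Rifabutin 300 mg/day without HAART" for Group I and "Rifabutin 150 mg/day every other day combined with PI containing HAART" for Group II. Section 4.6 confirms the 48-hour interval in Group II: "Patients of Group II treated with 150 mg of rifabutin every other day will undergo additional sampling at 48 hours".

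Section 4.6 lists the parameters: "AUC 0-24 h for all, AUC 0-48 h for Group II", plus Cmax and Tmax, which "will be determined directly from the data". It gives no dose-normalised AUC, apparent clearance or average concentration.

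The secondary objective reads: "To investigate the impact of protease inhibitors on the pharmacokinetics of rifabutin in Japanese HIV-infected patients". Section 4.7 begins "Differences between groups were determined by using the" and then assigns a test by type of data: Fisher's exact test for categorical variables and Mann-Whitney for continuous ones, at the 0.05 level. It does not name the pharmacokinetic parameter to be compared.

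**The concern.** PI use coincides completely with a change of dose and a change of interval. AUC0-24 covers a whole dosing interval in Group I but only the first half, in time, of the interval in Group II. If the one AUC available in both groups goes into the one between-group test given for continuous variables, the result is not an estimate of what PIs do to rifabutin clearance.

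The error can go either way. With no PI effect, the test would tend to show lower exposure with PIs. With strong inhibition of clearance, it could show no difference. Raw Cmax has the same weakness. At stake is the answer to the secondary objective, not the description of each regimen.

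**Working it through.** The plan has no figure of its own to reproduce here: the 10 patients per group rest on caseload, and no effect size, variability or power is given.

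**Inputs from the Protocol.** Group I: 300 mg every 24 h, or 600 mg per 48 h. Group II: 150 mg every 48 h. Ratio of dose per 48 h: 600/150 = 4. Ten patients per group; Mann-Whitney at 0.05.

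**Assumptions, because the Protocol gives none.** Linear kinetics, steady state, half-lives as shown, between-patient CV of 30%, 50% or 70%, a two-sided test.

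**Expected AUC0-24 ratio.** At steady state the AUC over one interval is dose/(CL/F). Let f be the share of Group II's AUC0-48 that falls in the first 24 h, and R the fold fall in CL/F caused by PIs. Then

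ratio II/I = (f × 150 × R)/300 = 0.5 × f × R.

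With rapid absorption and one-compartment disposition, f = 1/(1 + 2^(−24/half-life)), which lies between 0.5 and 1.

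| Half-life in Group II | f | Ratio if R = 1 (0.5f) | R that makes the ratio 1 (2/f) |
|---|---|---|---|
| 12 h | 0.800 | 0.40 | 2.50 |
| 16 h | 0.739 | 0.37 | 2.71 |
| 24 h | 0.667 | 0.33 | 3.00 |
| 45 h | 0.591 | 0.30 | 3.38 |
| 72 h | 0.558 | 0.28 | 3.59 |
| 100 h | 0.541 | 0.27 | 3.69 |
| Limits | 0.5 to 1 | 0.25 to 0.50 | 4 to 2 |

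With first-order absorption at 0.3 or 1.0 per hour, the no-effect ratio at 12 to 100 h is 0.27 to 0.39, so the result does not depend on the rapid-absorption form.

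If the half-life lengthens as clearance falls, a base half-life of 24 to 60 h becomes 96 to 240 h at R = 4. Then f = 0.543 to 0.517, and the ratio is 2 × f = 1.09 to 1.03. A four-fold fall in clearance would look like no difference.

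**Cmax.** In the same rapid-absorption model, peak concentration is proportional to dose/(1 − 2^(−interval/half-life)). With no PI effect, the raw Cmax ratio is again 0.5 × f. Dividing by dose leaves a ratio of f, between 0.5 and 1, because the interval still differs.

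**What the test would do.** These are simulated rejection rates for an exact Mann-Whitney test, 10 against 10 independent log-normal values, 20,000 trials per setting. Section 4.3 expects most patients to enter both groups. That affects the error rates but not the expected ratios above.

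| Parameter and truth | CV 30% | CV 50% | CV 70% |
|---|---|---|---|
| Raw AUC0-24, no PI effect (ratio 0.50 to 0.25) | 99.8–100% | 84–100% | 59–99% |
| Raw AUC0-24, PI effect that brings the ratio to 1 | 4.5% | 4.6% | 4.4% |
| Dose-normalised interval AUC, no PI effect | 4.4% | 4.4% | 4.2% |
| Dose-normalised interval AUC, two-fold PI effect | 99.7% | 83.7% | 58.7% |

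**Corrected parameters.** (AUC0-48/150)/(AUC0-24/300) = R, so the expected ratio is 1.00 with no PI effect at any half-life. Average daily exposure, AUC0-48/2 against AUC0-24, has expected ratio R/4, which correctly reflects the regimens.

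**Steady state.** Section 4.6 allows sampling after a minimum of five days. On alternate-day dosing that is about the third or fourth dose. Starting from no drug, the interval AUC at dose n is 1 − 2^(−48n/half-life) of its steady-state value: 75% (n = 3) to 84% (n = 4) at 72 h, and 34% to 43% at 240 h. A patient moving from Group I could instead carry over drug from daily dosing. At the third dose, the end-of-interval concentration would exceed the pre-dose one by a factor of 0.750/0.603 = 1.24 at 72 h and 0.340/0.242 = 1.40 at 240 h. Comparing the two is therefore an informative check.

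**The case against.** A reader might infer that the Protocol commits itself to testing raw AUC0-24 between groups. It does not. Section 4.7 assigns tests by data type, and section 4.6 only lists what will be calculated. The documents support a narrower statement: the parameter is not named, and the only AUC defined for both groups is unsuitable for the secondary objective.

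It can also be said that derived quantities such as CL/F belong in a statistical analysis plan, which is not shown. That has some force, and the data for the right analysis are already planned, since AUC0-48 is defined for Group II. But the Protocol itself fixes the list of parameters and the only between-group test for continuous variables. Applying that test to the common AUC gives a misleading answer, so this is more than a detail left for later.

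Raw exposure is a legitimate description of the two regimens and serves the primary objective. This objection stands in full.

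A reader might further infer that AUC0-24 grossly overstates average exposure in Group II. If PIs cut clearance three- to four-fold from base half-lives of 24 to 60 h, half-lives become 72 to 240 h, f is 0.558 to 0.517, and doubling AUC0-24 would overstate AUC0-48 by only about 3% to 12%. The Protocol never doubles it and calculates AUC0-48 directly. Nor is a significant drop certain when PIs have no effect: the rejection rate falls to 59% at a CV of 70% with f = 1.

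Finally, the corrected parameter depends on steady state, which five days of alternate-day dosing does not ensure. This stands as a limit on the remedy, but it does not make the raw comparison valid.

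**Conclusion.** The point holds for the secondary objective only, and should be fixed. A between-group test on raw AUC0-24 or raw Cmax cannot separate the PI effect from dose and interval. Given linear steady-state kinetics, the no-effect AUC0-24 ratio is 0.25 to 0.50 instead of 1, whatever the half-life, and 0.28 to 0.37 at assumed half-lives of 16 to 72 h. Equality of the raw values would correspond to a two- to four-fold fall in CL/F. The half-lives and CVs are assumptions; the 0.25 to 0.50 bound needs neither. No data are lost, because both full-interval AUCs can be calculated from the planned samples.

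**What to change.** In sections 4.6 and 4.7:

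- Name the parameter for the PI effect: dose-normalised AUC over each group's own interval, AUC0-24/300 mg in Group I against AUC0-48/150 mg in Group II, or equivalently apparent CL/F as dose divided by interval AUC.
- Compare average daily exposure as AUC0-24 in Group I against AUC0-48/2 in Group II, labelled as a comparison of regimens.
- Report Cmax both raw and dose-normalised, noting that dose-normalised Cmax still reflects the difference in interval. Keep Group II's AUC0-24 as descriptive.
- State that the PI-effect estimate assumes linear kinetics and steady state. Report each patient's days on the current regimen at sampling, and compare the pre-dose concentration with the end-of-interval one (24 h in Group I, 48 h in Group II) as a steady-state check.

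The cost is wording, recording of days on regimen, and slightly more analysis. The pre-dose, 24-hour and 48-hour samples are already scheduled, and no change of dose, schedule or sampling is implied. The remaining downside is that the corrected estimate still depends on the stated steady-state assumption.

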**4.7 Statistical analysis**

Differences between groups were determined by using the Fisher’s exact test for categorical data and the Mann Whitney’s test for continuous variables. For all statistical analyses, differences were considered significant if the *p* value was less than 0.05.

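### Most patients are expected in both groups, yet the named group tests assume independent samples, so the PI comparison is conservative and loses power

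*Protocol*

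**What the plan says.** Section 3 describes the study as "An open-label pharmacokinetic study with two arms" and says nothing about patients contributing to both.

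Section 4.3 plans 10 patients in Group I (rifabutin without HAART) and 10 in Group II (rifabutin with PI-containing HAART). The justification is accrual: "the average number of HIV-positive mycobacterium cases at NCGM is around ten per year", so that "at least 10 for each study arm is expected if the sequential enrollment of a patient into both groups is achieved in most participants". Section 4.4 gives the enrolment window as "from February 2008 and March 2009".

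Section 4.7 names the tests: "Differences between groups were determined by using the Fisher’s exact test for categorical data and the Mann Whitney’s test for continuous variables". Significance is set at p below 0.05, with sidedness not stated. No section mentions pairing or a within-patient analysis, or says how patients seen in one group only are to be handled.

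**The concern.** Mann-Whitney and Fisher's exact tests take the two groups as separate samples. By the protocol's own expectation, the groups are largely the same people measured twice. The tests then use the wrong reference distribution and leave between-patient variability in the error term, although the design would let most of the shared patients act as their own controls.

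The secondary objective, the effect of protease inhibitors on rifabutin pharmacokinetics, depends on this comparison, and Section 4.7 offers no other. With about 10 patients per group, a real effect could be missed and a non-significant result misread as no effect. An unseen SAP does not settle the matter, because the protocol did not leave the method open: it named the tests.

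**Working it through.** **1. How much overlap the plan needs.** Inputs: about 10 cases a year (Section 4.3) and a window of 13 to 14 months, depending on how the end months are counted (Section 4.4).

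- Distinct patients: 10 × 13/12 = 10.8 to 10 × 14/12 = 11.7. This is consistent with the planned 10 per group only if patients are shared.
- Filling 10 + 10 places needs 20 − 11.7 = 8.3 to 20 − 10.8 = 9.2 patients in both groups.

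This assumes that every case is eligible and consents. Fewer patients would mean more overlap or a smaller study.

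**2. What independence gets wrong.** With n = 10 per group, m shared patients, within-patient correlation ρ and common log-scale variance σ², the variance of the difference in means is (2σ²/n)(1 − mρ/n). An independent-sample analysis takes it as 2σ²/n. The ratio of true to assumed variance, for ρ = 0.3 / 0.5 / 0.7, is:

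- m = 10: 0.70 / 0.50 / 0.30
- m = 8: 0.76 / 0.60 / 0.44

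The assumed variance is too large, so the test rejects too rarely.

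**3. Actual type I error.** This was simulated with an exact two-sided Mann-Whitney test at nominal 5%, on normal data on the log scale. The protocol gives no ρ, so the values are assumptions.

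| Shared of 10 | ρ = 0 | ρ = 0.3 | ρ = 0.5 | ρ = 0.7 |
|---|---|---|---|---|
| 10 | 4.5% | 2.1% | 0.9% | 0.2% |
| 8 | 4.4% | 2.4% | 1.3% | 0.5% |

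Repeat simulations agree within noise (for example 1.7–2.1% with 10 shared at ρ = 0.3, and 0.4–0.5% with 8 shared at ρ = 0.7).

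**4. Power.** Assumptions: CV 40% and a true ratio of 1.5. The protocol gives neither.

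- σ = √ln(1 + 0.4²) = 0.385; effect = ln 1.5 = 0.405, or 0.405/0.385 = 1.05 SD.
- Paired t on k pairs: SD of a difference = σ√(2(1 − ρ)) = 0.456 / 0.385 / 0.298 for ρ = 0.3 / 0.5 / 0.7. The non-centrality is 0.405√k divided by that SD, on k − 1 degrees of freedom.
- k = 10: non-centrality 2.81 / 3.33 / 4.30.
- k = 8: non-centrality 2.52 / 2.98 / 3.84.

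| Shared of 10 | ρ | Mann-Whitney, all patients | Paired t, complete pairs only |
|---|---|---|---|
| 10 | 0.3 | 56% | 70% |
| 10 | 0.5 | 58% | 84% |
| 10 | 0.7 | 61% | 96% |
| 8 | 0.3 | 55% | 57% |
| 8 | 0.5 | 58% | 73% |
| 8 | 0.7 | 59% | 90% |

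The table holds simulated values; the non-central t calculation gives the paired-t figures to within about 1 percentage point. With 9 shared patients, close to the upper end of the accrual arithmetic, Mann-Whitney has 57% / 59% at ρ = 0.3 / 0.5 against 66% / 79% for a paired t on the nine pairs.

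**5. Precision.** With full overlap, the standard error of the paired difference is √(1 − ρ) times the independent-sample one: 0.84 / 0.71 / 0.55.

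**The case against.** - **Direction of error.** A reader might infer that using these tests risks false claims of a PI effect. The figures show the opposite under positive correlation, which is what one would ordinarily expect of two measurements of one drug in one patient. A significant Mann-Whitney result would stand; only a null result is hard to read. This stands in full.
- **A paired test is not always better.** A reader might carry the full-overlap gain over to the study as planned. Section 4.3 says only that most participants are shared, and makes even that conditional. With 8 pairs at ρ = 0.3 a paired t gains about 2 points (57% against 55%), and the signed-rank test on those pairs falls below Mann-Whitney (about 50%). With ρ = 0, Mann-Whitney is valid apart from its usual discreteness. This stands, and is why pairs-only tests should be the sensitivity analysis.
- **A mixed model can err the other way.** With 10 per group, a random-effect model judged by a normal-reference Wald test had a simulated type I error of about 5% to 11%, depending on overlap and the set of runs. Small-sample degrees of freedom are therefore part of the fix. Logging every parameter would also be wrong: Tmax takes only scheduled sampling times, and one of these is pre-dose.
- **Selection.** One might argue that patients who reach only one group bias the comparison. The protocol does not describe who they would be, and a mixed model also uses them, so the point does not rest on this.
- **Fisher's exact test.** The independence requirement applies here too, but this was not simulated. Section 4.7 names no binary endpoint or baseline test, and Section 4.5 collects adverse events continuously until two years after rifabutin stops, so no paired binary outcome per group is yet defined.

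**Conclusion.** The mismatch between Sections 4.3 and 4.7 is real and lies within the protocol. The groups are expected to share about 8 to 9 of 10 patients, and the named tests treat them as independent. With 8 to 10 shared patients, Mann-Whitney works at an actual level of about 2% / 1% / 0.2–0.5% for ρ = 0.3 / 0.5 / 0.7. Its power is about 55–61%, where a paired t reaches 57–70% / 73–84% / 90–96%. The loss is material at ρ of 0.5 or more. At ρ = 0.3 it runs from almost nothing with 8 pairs to about 14 points with 10.

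These sizes rest on assumed ρ, CV 40%, a true ratio of 1.5, log-normality and two-sided testing.

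Two stronger readings are not supported. The study as a whole is not invalidated: the primary objective is to evaluate pharmacokinetics in this population, and no between-group test is tied to it. Nor does pairing turn the contrast into a pure PI effect, since the groups also differ in rifabutin dose and schedule. This should be fixed, but it concerns the secondary objective only.

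**What to change.** **Section 3.** State that a patient may contribute to both groups in sequence, and that some may contribute to one only.

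**Section 4.7.**

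- For AUC and Cmax, replace Mann-Whitney with a linear mixed model on log-transformed values: group as fixed effect, patient as random effect, and small-sample degrees of freedom such as Kenward-Roger. Report the geometric mean ratio with its 95% CI. This uses both shared and single-group patients.
- Add a paired t or Wilcoxon signed-rank test on complete pairs as a sensitivity analysis, and report the number of pairs.
- Analyse Tmax unlogged, by signed-rank on the pairs.
- Do not apply Fisher's exact test to categorical outcomes as if patients in both groups were independent. Where a paired binary outcome exists, define it for each group and use an exact McNemar test.

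**Cost.** Wording in two sections, with no extra patients or blood samples. The analysis needs each patient's records linked across the two groups, which the unique codes in Section 5.3 should allow if one code is kept per patient. It also takes on a distributional assumption on the log scale that Mann-Whitney does not make; the signed-rank result on complete pairs gives a check on it.

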**5. ETHICAL CONSIDERATIONS**

**5.1 Ethics Committee**

This study will be conducted in accordance with the ethical principles that have their origin in the Declaration of Helsinki and applicable regulatory requirements that prescribed in "Ethics Guidelines for Clinical Research" (July 30, 2003, Ministry of Health, Labor and Welfare) in Japan. Prior to the study, the investigator must have written and dated approval opinion from the IRB/EC of all of the NCGM for the protocol, consent form and any other written information to be provided to subjects.

**5.2 Informed Consent**

Investigators must ensure that participants are clearly and fully informed about the study. Participants will be told that they are free NOT to participate in the study and reassured that this will not affect their care in any way.

**5.3 Confidentiality**

Data obtained from participants during study shall be treated with absolute confidentiality. Individual names, chart numbers and addresses are omitted from Case report form (CRF) and questionnaires and the unique codes will be used in the study. CRFs will be stored in a locked cabinet at ACC office and will be destroyed when the study is completed. When the results of the study will be published at the academic conferences or in the scientific journals, privacy of the participants is completely protected.

**6. ADMINISTRATION SECTION**

**6.1 Compliance with the Protocol**

This study shall be conducted in this approved protocol. The investigator should not implement any deviation or change to the protocol without prior review and documented approval/favorable opinion from the IRB/EC of an amendment.

**6.2 Records and Reports**

Investigators are required to prepare and maintain adequate and accurate case histories to record all observations. Documents must be consistent with the source documents or discrepancies must be explained.

**6.3 Budget**

This study will be financially supported by the Health Labour Sciences Research Grant (#H18-AIDS-008) from the Ministry of Health, Labour and Welfare, Government of Japan.

The cost for the examination of blood concentration level of rifabutin stated in the protocol will be covered within the research fund but not the cost of rifabutin and routine laboratory examination will not.

